### Participants

The sample size is based on the ISI. After 8 weeks of intervention, the mean ISI score baseline changes are approximately –7.7 (4.18) [21,32]. Assuming that the ISI score of the acupuncture group is slightly lower than that of the CBT group after 8 weeks of treatment, the ISI score should be no more than –2, with a noninferior effect threshold of –4 [33]—assuming that the single-side significant level is α=.025, power of the trial is 1 – β=.80, and the ratio between the EA group and the CBT-I group is 1:1. As calculated by PASS software (IBM Corp), each group requires 71 cases. Assuming that the dropout rate is 10%, the final sample size should be 160.

Eligible patients will be randomly assigned to either the EA or CBT-I group and will receive EA treatment or CBT-I consultation, respectively. The inclusion criteria are the International Classification of Sleep Disorders (Third Edition) criteria for insomnia disorder; women aged 40-60 years; according to STRAW+10 (Stages of Reproductive Aging Workshop + 10), signs of menopausal tendency that began to appear from clinical features, endocrinology, and biology until 1 year after final menopause; insomnia lasting for >3 months; total ISI score >14; and willingness to participate in the investigation and provide written informed consent prior to the trial.

The exclusion criteria are the use of menopause hormone therapy and sedative or antianxiety drugs; nonnatural menopause (due to surgery, radiation, and medication); any diseases that cause sleep disturbance; unknown causes of vaginal hemorrhage; diagnosis of mental disorders or any serious physical illness; receipt of CBT or acupuncture for insomnia; participation in any other clinical trial within the last 6 months; and pregnancy or lactation.

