### Outcome Measures

The primary outcome will be a mean change in total ISI from baseline to the end of the 8-week intervention. The validated ISI that has a concise design, good reliability, and has become a recognized tool for clinical researchers to evaluate the efficacy of insomnia will be used [35,36]. The ISI is a self-reporting questionnaire, and 7 self-rated items are included that evaluate the severity and impact of insomnia on patients. The total ISI score ranges from 0 to 28 points. The higher the score, the more serious the degree of insomnia, which is classified according to the total score (0-7 points represent clinically nonsignificant insomnia, 8-14 points represent subthreshold insomnia, 15-21 points represent moderately severe clinical insomnia, and 22-28 points represent severe clinical insomnia).

The secondary outcomes include the Menopause-Specific Quality of Life (MENQOL); Menopause Rating Scale; PSQI; Hamilton Depression Scale (HAMD); Hamilton Anxiety Scale (HAMA); hot flash score; and the level of estradiol, follicle-stimulating hormone, and luteinizing hormone in serum. Sleep architecture will be assessed using deep learning on polysomnograms (PSG). The ISI and MENQOL are measured at randomization and 4, 8, 12, and 20 weeks after randomization. The other outcomes are measured before and 8 weeks after randomization.

Menopause Rating Scale is a reliable method to measure the severity of menopausal compliance and contains 11 items in 3 dimensions (psychological, somatic-vegetative, and genitourinary systems). Each symptom is given a score of 0, 1, 2, 3, and 4 according to severity; the total is the sum of the scores of each item [37,38].

The PSQI scale is used to assess the quality of sleep during the previous month [39]. The scale consists of 9 questions, and the overall score ranges from 0 to 21. The higher the score, the worse the sleep quality. PSQI can be used to calculate patient sleep onset latency, time in bed, wake after sleep onset, total sleep time, sleep efficiency, and record the medicine used. Therefore, the combination of sleep quality and quantity can be used to assess sleep conditions and identify any sleep disorders.

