### Statistical Analysis

If statistical demographic data and other baseline characteristics are continuous variables, they will be represented by the mean (SDs) and median (IQR) values. We will also include count and grade data for frequency and composition ratios. Concomitant medications will be categorized using the Anatomical Therapeutic Chemical code, percentage of patients with concomitant medications, and the incidence of AEs will be compared using the *χ*^2^ test or Fisher precision probability.

After 8 weeks of intervention, the change in the ISI score will be compared with the baseline. The subgroups and baseline are used as covariates to compare the differences between groups by analysis of covariance and the 2-sided 95% CIs of the least squares mean differences between groups. During each visit, the ISI score will be recorded, and mixed-effects model repeated measures will be used to compare the differences between groups. To compare 2 independent samples, a 2-tailed *t* test or nonparametric test will be used for continuous data, and chi-square or Fisher exact or nonparametric tests will be used for categorical data. The times and number of drugs that are taken by participants will be compared between groups using a rank sum test. When a covariance analysis is used for the primary efficacy indicator, missing values will be filled using the last observation carried forward method. When using the mixed-effects model repeated measures method for analysis, the missing data will not be filled. When an outlier is found, the main researcher, the applicant, and the statistician will discuss the processing method together before the database is locked. If necessary, the outlier value will be removed for sensitivity analysis.

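### Secondary continuous outcomes appear to be left to unadjusted two-sample tests although each has a baseline value: valid under randomization, but less precise than the adjusted analysis planned for ISI

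*Protocol article*

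**What the plan says.** Three parts of the protocol article bear on this.

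- **Adjusted methods, Statistical Analysis.** The paragraph opens with ISI: "After 8 weeks of intervention, the change in the ISI score will be compared with the baseline". The next sentence reads "The subgroups and baseline are used as covariates to compare the differences between groups by analysis of covariance", with 95% confidence intervals for the adjusted mean differences. The mixed model is also tied to ISI: at each visit "the ISI score will be recorded, and mixed-effects model repeated measures will be used to compare the differences between groups".
- **Unadjusted methods, same section.** For comparing two independent samples, a two-tailed t "test or nonparametric test will be used for continuous data". No covariate is named. No sentence gives an adjusted method for a named secondary outcome.
- **Schedule, Outcome Measures and Table 1.** "The ISI and MENQOL are measured at randomization and 4, 8, 12, and 20 weeks after randomization". For the remaining outcomes, "The other outcomes are measured before and 8 weeks after randomization". Table 1 agrees: MENQOL, PSQI, Menopause Rating Scale, HAMA, HAMD, hot flashes, polysomnography and serum hormones all have a baseline assessment.

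**The concern.** The plan treats similar data in two ways. For ISI it uses the baseline value. For the other continuous outcomes it states only a comparison that need not use it, although the value will be collected. MENQOL shows this most clearly, because it has the same visit schedule as ISI but no repeated-measures model.

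What is at stake is precision on the supportive endpoints. There is also an avoidable error whenever the groups differ by chance at baseline: a comparison of week-8 scores carries part of that difference through, and a comparison of change scores over-corrects for it.

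**Working it through.** **Inputs.** The sample-size paragraph under Participants gives SD 4.18 for ISI change, an assumed difference of 2 against a margin of 4, one-sided α 0.025, power 0.80, 71 per group, 10% dropout and 160 in total. The article gives no correlation between baseline and follow-up for any secondary outcome, so r = 0.3, 0.5 and 0.7 is an assumption.

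**The plan's own figure.** n per group = 2 × (1.96 + 0.8416)² × 4.18² / (4 − 2)² = 68.6, so 69. The noncentral t gives 70 (power 0.803), and 71 gives power 0.808. For dropout, 71 / 0.9 = 78.9, so 79 per group or 158. The stated 71 and 160 are reproduced to within rounding. This calculation concerns ISI only, and the present point does not change it. It supplies n = 71 per group for what follows.

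**Variance of the group difference.** Take a comparison of means with equal variances at both visits, and set the variance for week-8 scores to 1:

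- week-8 score: 1
- change score: 2(1 − r)
- ANCOVA: 1 − r²

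ANCOVA relative to the week-8 score is therefore 1 − r². Relative to the change score it is (1 − r²) / [2(1 − r)] = (1 + r)/2.

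| r | ANCOVA ÷ week-8 t test | ANCOVA ÷ change t test | n per group to match ANCOVA at 71: week-8 | same: change |
|---|---|---|---|---|
| 0.3 | 0.91 | 0.65 | 71/0.91 ≈ 78 | 71/0.65 ≈ 109 |
| 0.5 | 0.75 | 0.75 | 71/0.75 ≈ 95 | 71/0.75 ≈ 95 |
| 0.7 | 0.51 | 0.85 | 71/0.51 ≈ 139 | 71/0.85 ≈ 84 |

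**The same in terms of power.** At 71 per group, a week-8 t test has 80% power for a difference of (1.96 + 0.8416) × √(2/71) = 0.47 SD. For that difference, at r = 0.3, 0.5 and 0.7, ANCOVA has 83.6%, 89.9% and 97.5% power. A change-score t test has 65.8%, 80.0% and 95.1%.

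**Error conditional on imbalance.** One standard error of the baseline difference is √(2/71) = 0.168 SD. With an imbalance of that size:

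- the week-8 estimate shifts by r × 0.168 = +0.05, +0.08 and +0.12 SD
- the change estimate shifts by (r − 1) × 0.168 = −0.12, −0.08 and −0.05 SD
- ANCOVA removes the shift

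**Check by simulation** (20,000 trials, 71 per group). The unadjusted variance divided by the ANCOVA variance was 1.09, 1.33 and 1.95 for week-8 scores and 1.53, 1.32 and 1.17 for change scores. The formulas give 1.10, 1.33, 1.96 and 1.54, 1.33, 1.18. Averaged over all trials, every estimator had a bias of about zero. Among trials with a baseline difference above one standard error, the unadjusted estimates were off by 0.08 to 0.18 SD in absolute value, and ANCOVA by about 0.00.

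**The case against.** **The text may not assign these tests to the secondary outcomes.** The t-test sentence is generic and names no outcome. It could be a default for baseline or incidental comparisons, and a condensed article may leave the secondary models to an analysis plan that is not shown. This stands as a caveat: the link is an inference. It is a reasonable one, because once ANCOVA and the mixed model are tied to ISI, this is the only method that the article states for other continuous data.

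**The unadjusted tests are not wrong.** This stands in full. A reader might infer that the secondary estimates will be biased or the type I error inflated. Neither follows in a randomized trial, since the error described above exists only conditional on an observed imbalance.

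**The size is assumed.** This also stands. At r = 0.3 with week-8 scores, ANCOVA saves only 9% of the variance. The ratios apply to comparisons of means. They do not describe rank tests or a five-visit analysis of MENQOL, so no figure is claimed for either.

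**Two stronger readings go beyond the text.** One is that secondary results will come as P values without effect estimates. The article does not say so; a t test yields a mean difference and interval, and a rank test can be paired with a Hodges-Lehmann shift estimate. The other is that nonsignificant secondary results will be read as showing no difference. The article proposes no noninferiority or equivalence claim on a secondary outcome, and baseline adjustment would not by itself prevent such a reading.

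**Conclusion.** The point holds as a free improvement limited to the secondary outcomes. If the generic sentence governs them, the plan passes over baseline values that it will already have. For r between 0.3 and 0.7, ANCOVA variance is 9% to 49% lower than that of a week-8 t test and 15% to 35% lower than that of a change-score t test. The article does not say which score the t test would use, but precision is lost either way for any r strictly between 0 and 1. For MENQOL the argument is one of consistency with ISI rather than a computed gain. The noninferiority conclusion on ISI does not depend on any of this, because ISI already has an adjusted analysis.

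**What to change.** Before database lock, prespecify the following:

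- **Two-visit secondary outcomes:** ANCOVA of the week-8 value on treatment and the outcome's own baseline, reporting the adjusted difference with its 95% CI.
- **Skewed outcomes (hot flash score, hormones):** the same model on a log or other transformation fixed in advance. The hot flash score can be zero, so a plain log may not serve.
- **MENQOL:** the same mixed model as for ISI, including the baseline value.
- **Rank tests:** sensitivity analyses only.

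State also which outcomes the generic two-sample sentence is meant to cover. The cost is wording in the analysis plan. No visit, measurement or participant is added, since every baseline value is already scheduled.

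### Carrying the last ISI forward in the primary ANCOVA can shrink the EA versus CBT-I difference and, if dropout is similar in both arms, raises the false-noninferiority rate above 2.5%

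*Protocol article*

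**What the plan says.** The Outcome Measures section of the protocol article defines the primary outcome as the mean change in total ISI from baseline to the end of the 8-week intervention. The same section and Table 1 place ISI at baseline and at weeks 4, 8, 12 and 20.

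The Statistical Analysis section plans an ANCOVA of the week-8 change with a two-sided 95% CI for the between-group difference. For that analysis of the primary indicator, "missing values will be filled using the last observation carried forward method". The section also plans a repeated-measures mixed model for ISI across visits, and there the rule is different: "When using the mixed-effects model repeated measures method for analysis, the missing data will not be filled". The only sensitivity analysis it names concerns outliers.

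The Participants section sets the test: "assuming that the single-side significant level is α=.025", "with a noninferior effect threshold of –4". It allows for 10% dropout and gives no split by arm.

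**The concern.** The only ISI values that can be carried forward to week 8 are those from baseline and week 4. A participant who leaves before week 4 therefore enters the primary analysis with a change of exactly zero, and one who leaves later enters with a mid-course change. Each arm mean moves toward zero in proportion to its own dropout and its own true change.

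In a superiority trial, a shrunken difference usually costs power. In a noninferiority trial it works the other way: if EA is truly worse by the full margin, shrinkage makes EA look closer to CBT-I than it is. What is at stake is the one-sided 2.5% error rate behind the trial's main claim.

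**Working it through.** **Inputs from the Participants section.** "the mean ISI score baseline changes are approximately –7.7 (4.18", with the bracketed figure read as the SD; an assumed true disadvantage of 2 points ("the ISI score should be no more than –2"); margin 4; one-sided alpha 0.025; "power of the trial is 1 – β=.80"; "the ratio between the EA group and the CBT-I group is 1:1"; 71 per group; 10% dropout; 160 in total.

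**1. The plan's own figure.** n per group = 2 × (1.960 + 0.842)² × 4.18² / (4 − 2)² = 68.6, so 69; the noncentral t gives 70. The stated 71 is reproduced within 2. Then 71 / 0.9 = 78.9, so 79 per group and 158 in total, against a stated 160. The sample size is not at issue, and its inputs can be used below.

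**2. Expected LOCF difference at the margin.** Take the difference as EA change minus CBT-I change, so that positive means EA is worse. Assume that −7.7 is the CBT-I change; the article does not name the arm. A true difference of 4 then gives EA −7.7 + 4 = −3.7. Let dE and dC be the dropout proportions, unrelated to outcome, and let a be the average share of the week-8 change already present in the carried value (0 if baseline is carried). Then

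D = −3.7 × [1 − dE(1 − a)] + 7.7 × [1 − dC(1 − a)] = 4 − (1 − a)(7.7 dC − 3.7 dE).

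With equal dropout d this is 4 × [1 − d(1 − a)], which is always below 4 when a < 1.

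**3. Error rate.** With 80 per arm, SE = 4.18 × √(2/80) = 0.661. Noninferiority is declared when the upper 95% limit is below 4, so the false-claim rate is about Φ(−1.96 + (4 − D)/0.661).

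The share of the effect present at week 4 is not in the article; 60% and 90% are assumed. In the central case half of the dropouts leave before week 4, so a = 0.5 × 0 + 0.5 × 0.6 = 0.3.

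| Dropout EA / CBT-I | Timing and week-4 share | a | D | (4 − D)/SE | Φ formula | Simulated |
|---|---|---|---|---|---|---|
| 10% / 10% | all after week 4, 90% | 0.9 | 3.96 | 0.06 | 2.9% | about 3% |
| 10% / 10% | all after week 4, 60% | 0.6 | 3.84 | 0.24 | 4.3% | about 4% |
| 10% / 10% | half early, 60% | 0.3 | 3.72 | 0.42 | 6.2% | about 6% |
| 10% / 10% | all before week 4 | 0 | 3.60 | 0.61 | 8.8% | 8.0-8.9% |
| 5% / 15% | half early, 60% | 0.3 | 3.32 | 1.03 | 17.5% | 16-17% |
| 15% / 5% | half early, 60% | 0.3 | 4.12 | −0.18 | 1.6% | 1.5-1.7% |
| 20% / 10% | half early, 60% | 0.3 | 3.98 | 0.03 | 2.7% | 2.6-2.8% |

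The last column gives the range over separate simulations, each with at least 6,000 replicates per scenario. Under the same dropout with nothing filled, the simulated rate is 2.3-2.7%.

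**4. Break-even.** D = 4 when 7.7 dC = 3.7 dE, that is, when EA dropout is 7.7/3.7 = 2.1 times CBT-I dropout. Below that ratio LOCF favours noninferiority; above it, LOCF works against it.

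**5. Effect at the planned difference.** With a true difference of 2 and 10% dropout in each arm, LOCF raises the simulated chance of declaring noninferiority from 81% to 86-87%. That gain comes from the shrinkage and is not real power.

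**The case against.** A reader might infer that LOCF always pulls the arms together here. The article does not support that. It gives one overall dropout rate, and EA asks for 20 visits against 8 CBT-I sessions, so heavier EA dropout is quite possible. At 15% EA and 5% CBT-I the error falls below nominal, and at 20% and 10% it is about nominal. This part of the objection stands: the direction depends on the dropout in each arm. It does not rescue the rule, because error control that needs EA to lose at least twice as many participants as CBT-I cannot be relied on in advance.

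The size also rests on inputs the article does not give. If equal dropout falls entirely after week 4 and 90% of the effect is present by then, the error is about 3%, close to nominal. The unfilled comparison looks good partly because dropout was assumed unrelated to outcome; it does not show how the mixed model behaves if that fails. Bias is measured against the outcome had participants stayed to week 8. If leavers truly return to baseline and that outcome were the target, carrying baseline forward would not be biased in this way, but the article states no such target. These are fair limits on the figures.

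A reader might also infer that two analyses with different missing-data rules leave the choice open until after unblinding. That is weakly supported. The article ties the ANCOVA to the primary indicator and describes the mixed model for the ISI recorded at each visit, and ranking analyses is commonly left to an SAP, which is not shown. The planned mixed model is partial mitigation, but it does not alter the rule stated for the ANCOVA.

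**Conclusion.** The concern holds in conditional form. LOCF is the stated rule for the ANCOVA of the primary endpoint. With 10% dropout in each arm it cuts a true difference of 4 to between 3.60 and 3.96 and raises the one-sided error from 2.5% to roughly 3-8%, depending on when participants leave and how much of the effect is present by week 4. The inflation is larger if CBT-I loses more participants, and it vanishes or reverses once EA dropout reaches about twice that of CBT-I.

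The figures rest on −7.7 being the CBT-I change, an SD of 4.18 in both arms, dropout unrelated to outcome, a week-4 share of 60-90%, and a target effect defined as if participants had stayed to week 8. That LOCF fails to protect the error rate under the plainest reading of the protocol's own dropout figure is well supported; the exact size is not.

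**What to change.** Replace LOCF in the primary analysis. The simplest route is to name the already planned unfilled mixed model, with its week-8 between-group contrast and 95% CI set against the 4-point margin, as the primary analysis. ANCOVA after multiple imputation is an acceptable alternative. Keep LOCF at most as a sensitivity analysis. Add one sensitivity analysis that shifts missing EA outcomes toward inferiority, since neither main option protects against dropout that depends on the unseen outcome. Report dropout by arm and by timing (before or after week 4), so that the reader can judge the direction of any remaining bias.

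The cost is a change of wording before the database is locked and a little programming. No new data, visits or participants are needed. Apparent power will be lower than LOCF would show (81% rather than 86-87% at the planned difference), but 81% still meets the 80% target.

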## Results

Recruitment of participants for the study is presently underway. The inaugural participant was enrolled in January 2023, signifying the commencement of the recruitment phase. It is anticipated that the recruitment process will persist until January 2025, at which juncture data collection will commence.

## Discussion

### Principal Findings

This will be the first randomized, noninferiority, EA-controlled trial to study the efficacy and safety of EA compared with CBT for PMI. Considering that drugs may cause adverse reactions such as feeling drowsy, lightheaded, and dizzy, medications need to be limited to the lowest necessary dose and shortest necessary duration and nonpharmacological therapies are reasonable to use [18].

CBT-I has a longer duration of treatment and is suitable for patients with cognitive impairment [46]. It is offered in various forms such as one-on-one or in groups via telephone, the internet, or books. During the COVID-19 pandemic, some evidence-based psychotherapy was provided to medical staff to relieve mental pressure and prevent the occurrence of psychological disorders [47]. Web-based CBT has been shown to be effective in treating and preventing many stress-related symptoms among health care workers. Web-based CBT has also shown strengths in breast cancer survivors with clinically significant sleep problems [48].

Actigraphy (ACT) and PSG are commonly used to monitor sleep in clinical studies [49]. We have chosen PSG to monitor sleep as an objective efficacy index, as it makes a comprehensive estimation by monitoring various physiological parameters such as EEG, electromyogram, ECG, respiratory airflow, respiratory motion, and oxygen saturation while being manually analyzed by a sleep technician. Thus, sleep architecture is shown without bias. In addition, PSG is the gold standard for the assessment and diagnosis of sleep disorders [50]. However, PSG must be performed in the laboratory under the supervision of a relevant technician, and the discomfort of the electrodes and harnesses necessary for PSG monitoring brings about the “first night effect” [51], which also has a higher cost than other tests. Rather than recording EEG activity, ACT combines body movement frequency with the help of gravity sensors [52]. Although ACT is economical and simple to wear, it has a distinct drawback in that it may overestimate sleep time and underestimate wake time [53].

Women who are undergoing menopause transition seem to report more sleep difficulties. The content of some hormone changes dramatically in this stage, which may be associated with decreased melatonin synthesis and secretion. Progesterone reduces arousal and can have a sedative effect, while estrogen increases the turnover of the neurotransmitter norepinephrine and, subsequently, increases time spent in REM sleep and decreases REM latency [54]. Many of the menopausal symptoms (eg, hot flashes and night sweating) are precipitating factors for insomnia, which are in relation to the occurrence of poor sleep quality in menopausal women. Hot flashes are one of the most typical menopausal symptoms and are highly associated with awakening perimenopausal women in particular [55]. Repeated exposure to menopausal symptoms that cause wakefulness at night may perpetuate insomnia symptoms through conditioned arousal.

